### Study design and setting

This is a prospective, pragmatic, assessor-blinded, superiority randomised controlled trial evaluating participants who have been diagnosed with knee OA and are considering TKA. Participants will be recruited from two sources: St. Vincent’s Hospital Melbourne (SVHM) Orthopaedic Outpatient Clinic and HCF (private health insurance company) client base across Australia.

From the SVHM source, patients who have been referred to an orthopaedic surgeon for consideration for TKA will be targeted for recruitment. This information can be found on clinic appointment lists in advance of 3 months. Patients who are referred to the clinic often wait up to 1 year to be seen by an orthopaedic surgeon. Following consultation, if deemed appropriate for surgery, patients may wait for another 6–12 months before the surgery is performed. Often, patients who are seen at SVHM are already in the later stages of the TKA journey as a product of resource constraints and waiting lists at the hospital.

In comparison, patients from the HCF source are at various stages of the TKA journey. As expected, some patients may be very early in disease progression, with symptoms being adequately managed by their general practitioner (GP). However, other patients may be more advanced in their disease progression and may have already made an application for TKA funding. Potential participants here will be recruited from internal advertising.

Having a diverse recruitment pool with patients at all stages of the TKA journey can help us evaluate the optimal timepoint for *SMART Choice* tool usage. We hypothesise that patients earlier in the TKA journey may be more open to decision making with consideration of predicted outcomes. In contrast, patients who are further along the TKA journey may feel too invested for the tool to influence decision making around willingness for surgery. The optimal timepoint for *SMART Choice* tool usage will be evaluated from a sub analysis of patients at different timepoints in the TKA journey.

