### Outcomes

The primary outcome for this study is the impact of the *SMART Choice* tool on patient willingness to undergo surgery. This will be measured using a binary question asking the patient if they would be willing to have TKA due to their knee symptoms, as described in Table 2.

**Table 2 Tab2:** Schedule of Assessments (SoA)

	SCHEDULE OF ASSESSMENTS						
	Enrolment	Allocation to intervention	Post-allocation				Close-out
**TIME POINT**	***t***_***x***_	**t**_**0**_	***t***_***1***_	***t***_***2***_	***t***_***3***_	***t***_***4***_	***t***_***y***_

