**ASSESSMENTS:**							
**Baseline questionnaire**		X					
**Willingness for surgery**		X		X	X	X	X
**Already proceeded with surgery**				X	X	X	X
**Qualitative questionnaires **						X	X

See also Table 3 for definitions and timepoints. I = intervention group. TAU = treatment as usual group. X = participants in both intervention and treatment as usual groups

The secondary outcomes for this study include:Determining the optimal timepoint for prognostic tool use in a patient’s TKA journey to maximise the effect on willingness to undergo surgery.Determine whether there are differences in the effectiveness of the *SMART Choice* tool when used in subpopulations such as sex, gender, and ethnicity.Understanding the user experience and effect on decision making of the *SMART Choice* tool through decision quality questionnaires.

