	***t***_***3***_	12 weeks after initial assessment (t_0_)
	***t***_***4***_	6 months after initial assessment (t_0_)
	***t***_***y***_	Time at study closure for individual participant. This should be equal to t_4_ if all assessments are completed on schedule.
Baseline Questionnaire	Questionnaire for all patients who have been allocated in the study. Same for all groups. Captures basic demographic data as well as questions about previous knee treatment and surgery. This section will also capture baseline health-related quality of life through the VR-12 and EQ-5D-3L.	
Wilingness for Surgery	This assessment asks the question "Are your knee symptoms so bothersome that you wish to undergo surgery if medically fit to do so?" Yes / No. If yes, "In what time frame are you willing to have surgery?" [Time in months].	
Already Proceeded with Surgery	This assessment asks the question "Have you already received a TKA for your knee symptoms?" Yes / No. The purpose for this assessment is to 1) check if the patient has undergone TKA, and 2) outcome aligns with their willingness for surgery response.	
Qualitative Questionnaires	This assessment consists of K-DQI (decision quality) and SURE (decisional conflict) tools.	

*PIS* participant information sheet, CF consent form, *TKA* total knee arthroplasty, *OA* osteoarthritis, *VR-12* Veterans-RAND 12, *EQ-5D-3L* EuroQol 5 Dimensions 3 Levels, *K-DQI* Knee Decision Quality Instrument, *SURE* decisional conflict screening tool

The initial assessment will be the first timepoint at which regular assessments will be performed. At the end of the initial assessment, participants will be thanked for their time and be reminded of follow-up. Participants will receive emails with access to the study portal at subsequent follow-up periods: 6 weeks, 3 months, and 6 months after recruitment.

Willingness for surgery assessment consists of a single binary question: “Are your knee symptoms so bothersome that you would be willing to undergo surgery if medically fit to do so? (Yes/No)” If yes, “In what time frame are you willing to have surgery?” [Time in months]. The purpose of this assessment is to evaluate whether the patient is still of the mindset to proceed with surgery.

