Already proceeded with surgery assessment consists of a single binary question: “Have you already received a TKA for your knee symptoms? (Yes/No).” The purpose of this assessment is to 1) correlate true outcomes for willingness for surgery if applicable and 2) differentiate baseline HRQoL data between knee OA symptoms (if not proceeded with surgery yet) or TKA outcomes. This will not be asked at the initial assessment.

All participants in the intervention group will be sent two additional decision quality questionnaires via email at the time of their final assessment (6 months after recruitment). These questionnaires have been validated from previous research to produce discriminatory and reproducible results [29, 30]. The addition of these questionnaires will provide a cross-sectional understanding of how useful the *SMART Choice* tool was for patient decision-making.

The first questionnaire is the “Knee Osteoarthritis Decision Quality Instrument” (K-DQI) [29]. This questionnaire is specific for patients who suffer from knee osteoarthritis. The questionnaire aims to assess:Which aspects of decision-making matter most to the patientHow well the patient is understanding the information provided, andThe level of communication between the patient and clinician prior to decision-making.

The second questionnaire is a short screening tool to assess decisional conflict [30]. It consists of four binary items using the acronym “SURE” (Table 4).

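### The primary willingness question is tied to current knee symptoms and is asked again after TKA, so participants who accepted surgery and improved are likely to count as unwilling

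*Protocol article*

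**What the plan says.** The Outcomes section of the Protocol article defines the primary outcome as willingness for surgery: "This will be measured using a binary question asking the patient if they would be willing to have TKA due to their knee symptoms". The section on participant timeline and assessments words the item as "Are your knee symptoms so bothersome that you would be willing to undergo surgery if medically fit to do so". Table 3 has a slightly different version, "Are your knee symptoms so bothersome that you wish to undergo surgery if medically fit to do so". Both versions depend on how bothersome the knee is at the time of asking.

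Table 2 marks the willingness item at t0, t2, t3, t4 and ty. It marks the item on surgery already received at t2, t3, t4 and ty. The table key reads "X = participants in both intervention and treatment as usual groups". Follow-up falls at "6 weeks, 3 months, and 6 months after recruitment" (Table 3 gives 12 weeks for the second of these).

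The second item asks "Have you already received a TKA for your knee symptoms". Table 3 gives its purpose as recording whether TKA has occurred and checking that the "outcome aligns with their willingness for surgery response". The main text adds correlation with true outcomes and interpretation of the quality-of-life data. Neither place uses it to code the primary outcome.

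The Statistical plan analyses willingness by intention to treat, so operated participants stay in the comparison. Surgery during follow-up is foreseen: usual care includes performing TKA where appropriate, and some HCF participants "may have already made an application for TKA funding".

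**The concern.** Before surgery, Yes means the participant wants the operation. After a successful operation the same question invites No, because the symptoms it refers to have gone. The participant who acted on their willingness is then recorded with those who never wanted surgery. The stated aim of the item is to learn whether the patient still intends to proceed, and the Background uses willingness as a stand-in for the decision to have TKA. For operated participants the recorded answer can say the opposite of both.

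Two consequences follow. If surgery is equally common among willing participants in both arms, the observed difference shrinks in proportion and power is lost. If the tool changes how many willing participants go on to surgery, the error differs by arm. The comparison is then biased in a way that a larger sample does not remove. In particular, a tool that raised surgery uptake without changing willingness could appear to reduce willingness.

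**Working it through.** **Inputs from the Protocol article (Sample size and recruitment; Randomisation, allocation, and blinding).** Willingness 65% versus 50%; 169 per arm before inflation; two-sided 5% level; 80% power; 1:1 allocation.

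**Input not in the document.** f, the share of willing participants who have TKA before the assessment and then answer No. It is assumed here to lie between 5% and 30%.

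**Formula.** Normal approximation for two proportions, with p̄ the mean of p1 and p2:

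power = Φ{ [ |p1 − p2| − 1.96 √(2p̄(1 − p̄)/n) ] / √([p1(1 − p1) + p2(1 − p2)]/n) }

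**Step 1: reproduce the plan.** With p1 = 0.65, p2 = 0.50 and n = 169, the two standard errors are 0.0538 (pooled) and 0.0532 (unpooled). Then (0.15 − 1.96 × 0.0538)/0.0532 = 0.84, so power is 79.9%. Solving for 80% gives 170 per arm (arcsine version 169.1). The stated 169 is reproduced.

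**Step 2: same f in both arms.** Observed Yes rate = true willingness × (1 − f), so the difference is 15 × (1 − f) points.

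| f | Yes rates | Difference (points) | Power at 169 per arm | n per arm for 80% |
|---|---|---|---|---|
| 0 | 65.0% vs 50.0% | 15.0 | 79.9% | 170 |
| 5% | 61.8% vs 47.5% | 14.25 | 75.1% | 191 |
| 10% | 58.5% vs 45.0% | 13.5 | 70.1% | 214 |
| 20% | 52.0% vs 40.0% | 12.0 | 60.1% | 270 |
| 30% | 45.5% vs 35.0% | 10.5 | 50.3% | 342 |

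**Step 3: f differs by arm, true willingness 65% versus 50%.**

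- TAU 10%, tool 5%: 58.5% vs 47.5%, 11.0 points, power 52.6%.
- TAU 20%, tool 10%: 52.0% vs 45.0%, 7.0 points, power 25.0%.
- TAU 10%, tool 20%: 58.5% vs 40.0%, 18.5 points, so the true 15-point difference is overstated.

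**Step 4: no true effect, willingness 65% in both arms.** With f of 10% in one arm and 20% in the other, the Yes rates are 0.65 × 0.90 = 58.5% and 0.65 × 0.80 = 52.0%. This is a spurious 6.5 points. With p̄ = 0.5525 the standard errors are 0.0541 and 0.0540, and (0.065 − 1.96 × 0.0541)/0.0540 = −0.76. The test therefore rejects about 22% of the time, against a nominal 5%.

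**Step 5: what an overall f implies.** The plan is to recruit 200 from SVHM and 200 from HCF. If SVHM contributed almost no TKA by 6 months and willingness were similar in the two sources (both assumptions), an overall f of 20% would need about 40% of willing HCF participants to be operated on, since 0.20/0.5 = 0.40. An overall f of 30% would need about 60%. The upper rows of the table are therefore demanding; 5% to 10% needs about 10% to 20% of willing HCF participants.

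**The case against.** The strongest reply is that the rule for coding answers after surgery may sit in the analysis plan, and the skip logic in the full protocol or the flow diagram, none of which is shown. The authors plainly thought about surgery during follow-up, because they placed the surgery item beside every follow-up willingness item, and nowhere do they say that No after TKA means unwilling. This does not remove the point. The article states positively what the primary outcome is and what the surgery item is for, and followed as written these give the wrong classification.

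Other parts of the reply stand and limit the claim:

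- A reader might infer that operated participants will answer No. The documents do not show this. Some may still have symptoms, answer in retrospect or skip the item; the Background itself cites up to 20% unsatisfied after TKA. Likely is as far as the text goes.
- A reader might infer that surgery within 6 months is to be expected. The article says only that some HCF participants may have applied for funding, and that others are very early in their disease. SVHM patients may wait 6 to 12 months after consultation, and the Background calls waiting for actual TKAs unfeasible.
- A reader might reach larger effects by taking surgery rates as shares of all participants. With 10% versus 20% of everyone operated on and equal willingness of 65%, the rates would be 55% versus 45% and the test would reject about 45% of the time. That changes the denominator from the one in Step 2 and should not be set beside it. On the common basis the figures are 6.5 points and about 22%.
- The false-positive case needs the tool to change surgery uptake without changing willingness. The document neither supports nor excludes this; it illustrates direction and is not a forecast.

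**Conclusion.** The point holds as a flaw in the stated primary endpoint. A participant who has had TKA since baseline and whose symptoms have resolved is likely to be scored as unwilling, and the item that would identify that participant is given no part in the endpoint.

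The size is uncertain because the document gives no 6-month TKA rate, and SVHM waiting times suggest that it may be low in that half of the sample. With equal assumed rates of 5%, 10% or 20% among willing participants, power falls from 80% to 75%, 70% or 60%. With rates that differ by arm the comparison is biased in either direction, for example by 6.5 points when there is no true effect. All these figures assume that every operated willing participant answers No, so they are upper values for a given surgery rate.

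**What to change.** Define the primary endpoint at each assessment as willing if the participant answers Yes, or reports TKA of the study knee received since baseline, at or before that assessment. Under this coding the planned 65% versus 50% contrast and the 169 per arm stand unchanged.

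In the portal, ask the surgery item first and have it name the study knee and the period since baseline, because the present wording specifies neither. Keep asking everyone the willingness item, with no skip for operated participants.

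Report the raw willingness answer in all randomised participants as a sensitivity analysis. An analysis restricted to unoperated participants is not a good substitute, because it selects on an event after randomisation that the tool may influence.

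The cost is one sentence in the endpoint definition, a small wording change to the surgery item and a change in item order. No new assessment is needed.

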### Randomisation, allocation, and blinding

Participants will be randomly allocated in a 1:1 ratio into two groups: intervention and treatment as usual (TAU). Allocation will be performed using a computer-generated simple randomisation schedule of consecutive patients. The randomisation will be embedded into the web-based platform that hosts the study portal. All participants who meet the eligibility criteria will be randomised.

Due to the nature of the study, participants will remain unblinded from their allocation group. However, limited disclosure of allocation groups will be applied to prevent participants who are allocated to TAU from proactively seeking out online prognostic tools to use. Investigators (excluding research assistants who will not be involved in data analysis) will remain blinded to the allocation group and identity of patients until after final data analysis is performed. Surgeons will be blinded to the allocation group of their patients and will have no influence on the outcome of allocation or intervention.

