**Fig. 2 Fig2:**
[figure not shown]
Flow diagram describing the study procedure. SVHM: St. Vincent’s Hospital, Melbourne; HCF: Hospitals Contribution Fund Australia; VR-12: Veterans RAND-12; EQ-5D-3L: EuroQol 5 Dimensions 3 Levels; TAU: treatment as usual; K-DQI: Knee Decision Quality Instrument; SURE: decisional conflict screening tool

All recruited participants will be asked to complete a baseline questionnaire within the study portal. This provides an understanding of the participant’s general characteristics. The questionnaire will capture contact details, date of birth, sex, height, weight, comorbidities, medications (analgesia), smoking status, time with knee OA symptoms (years), previous nonoperative management of affected knee OA symptoms, time with knee OA symptoms, consultation with an orthopaedic surgeon in the past, appointment to see an orthopaedic surgeon arranged, previous surgery, previous injury to the affected knee, and presence of contralateral TKA. The baseline questionnaire will also capture the VR-12 and the Euroqol 5 Dimensions 3 Levels (EQ-5D-3L) data to understand the baseline HRQoL utility score for each group.

For participants in the intervention group, the study portal will allow access to the *SMART Choice* tool and provide a predicted outcome for the participant. Inputs onto the tool will be captured electronically; however, the participant will have the option to download a copy of their results for personal reference. Participants in the TAU group will not have access to the *SMART Choice* tool or predicted outcome and will instead continue with the regular assessments for the remainder of the study.

Following the baseline questionnaire (or *SMART Choice* tool use for the intervention group), participants will be asked to complete regular assessments in accordance with the Schedule of Assessments (Tables 2 and 3). This will consist of “willingness for surgery”, “already proceeded with surgery”, and decision quality questionnaires.

**Table 3 Tab3:** Definitions for SoA

Terms	Definitions	
Time Point	***t***_***x***_	Time at initial contact via email with PIS, CF, and eligibiility screen. If a patient is eligible and consents, allocation will immediately follow this time.
	**t**_**0**_	Time at allocation with initial concurrent assessments.
	***t***_***1***_	Immediately after allocation, for prognostic tool use in TAU group.
	***t***_***2***_	6 weeks after initial assessment (t_0_)

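### The text sends the K-DQI and SURE to the intervention group only, Table 2 sends them to both groups, and following the text leaves the effect on decision making without a comparator

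*Protocol article*

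**What the plan says.** The article gives two instructions on who completes the decision quality questionnaires.

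- **Text, Participant timeline and assessments:** "All participants in the intervention group will be sent two additional decision quality questionnaires via email at the time of their final assessment", that is, at 6 months. The paragraph does not mention the TAU group. It then names the two instruments as the K-DQI and SURE.
- **Table 2 (Schedule of Assessments):** the row "Qualitative questionnaires" carries X at t4 and ty. The legend defines the code: "X = participants in both intervention and treatment as usual groups". A separate code, I, denotes the intervention group alone and is used on the row for tool use.
- **Table 3 (definitions), on that row:** "This assessment consists of K-DQI (decision quality) and SURE (decisional conflict) tools".

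The third secondary outcome, listed under Outcomes and measured through these questionnaires, is "Understanding the user experience and effect on decision making of the" SMART Choice tool. The Statistical plan compares categorical outcomes between groups by chi-squared test.

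**The concern.** An effect of the tool on decision making is a contrast. It needs either a group that did not use the tool or a measurement taken before its use. If the questionnaires go to the intervention group alone, the trial will have one set of scores at one time point, with nothing to show whether they differ from those under usual care.

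The loss could not be repaired afterwards. TAU answers at 6 months cannot be collected once that contact has passed, and all participants get free access to the tool when the study period ends, so later TAU answers could be contaminated.

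**Working it through.** No figure in the article is attached to this point, so the main check sets the statements side by side.

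**1. Are the text and the table about the same instruments?** Yes. Table 3 defines the row as the K-DQI and SURE, and the text describes the same two. The different labels (qualitative in the tables, decision quality in the text) do not separate them.

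**2. Could X be loose shorthand for one arm?** Not by the table's own legend. It has a distinct code for the intervention group and uses it where only that group is meant.

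**3. Where does the rest of the article point?**
- Participant timeline and assessments says "participants will be asked to complete regular assessments in accordance with the Schedule of Assessments (Tables 2 and 3"), and lists the decision quality questionnaires among those assessments without limiting them to one arm.
- The same section says TAU participants "will instead continue with the regular assessments for the remainder of the study".
- Intervention and comparison groups states that, apart from the tool, the arms are handled identically.

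Three statements therefore agree with Table 2, and the sentence on e-mailing the intervention group stands alone.

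**4. What comparison is left under each instruction?** Table 2 schedules the questionnaires only at t4 and ty, which coincide when assessments run on schedule. There is no mark at t0, t2 or t3.

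| Instruction followed | Between-arm contrast | Before/after contrast |
|---|---|---|
| Table 2 (both arms) | yes, at 6 months | none |
| Text (intervention only) | none | none |

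SURE gives a binary result: one or more negative answers is a positive screen. The planned between-group chi-squared test would apply to it, but cannot be run on one arm.

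**5. What would the two-arm comparison deliver?** Inputs: 200 enrolled per arm (Sample size and recruitment) and a follow-up target above 85% (Statistical plan), so 0.85 × 200 = 170 responders per arm. The article gives no prevalence of SURE positivity, so a range is assumed.

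Half-width of the 95% interval for a difference in proportions, with common prevalence p and n per arm: 1.96 × √(2p(1−p)/n).

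- p = 0.50: 1.96 × √(2 × 0.25/170) = 0.106
- p = 0.30: 1.96 × √(2 × 0.21/170) = 0.097
- p = 0.20: 1.96 × √(2 × 0.16/170) = 0.085

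The difference would be known to within about 8.5 to 10.6 percentage points. With one arm there is no difference to estimate.

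**The case against.** The strongest defence is that the article often describes the questionnaires as a descriptive look at tool users. The abstract ties them to the patient's experience of using the tool, the timeline section speaks of a cross-sectional view of its usefulness, and the Discussion links them to user experience. On that reading one arm is enough. This stands for the user-experience half of the outcome, but not for the half that names an effect on decision making.

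The main randomised comparison on decision making is also intact. The Background names willingness for surgery as the proxy for decision making, and it is collected in both arms. A reader might infer that the whole secondary objective, or the trial's evidence on decision making, is lost. The article does not support that.

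Nor is Table 2 certain to be the correct version. Table 3 contains another arm-label slip: it assigns tool use at t1 to the TAU group, against the code I in Table 2. The X could be the mistake, so both repairs must stay open. The SURE items in Table 4 are not legible in the copy reviewed, so whether each can be answered without having used the tool could not be checked. The K-DQI, as described, covers patient priorities, understanding and communication with the clinician, none of which requires the tool.

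A reader might also infer that one-arm questionnaires defeat the statement that investigators "will remain blinded to the allocation group and identity of patients until after final data analysis is performed". That goes too far. Tool inputs are already captured in the intervention arm only, so arm-revealing data exist under either instruction and have to be kept from blinded analysts anyway. Questionnaire fields can be withheld in the same way.

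**Conclusion.** The contradiction is real and lies within the current text. Its consequence is conditional and partial. If Table 2 is implemented, the defect is one wrong sentence. If the text is implemented, the effect-on-decision-making part of the third secondary outcome has neither a between-arm nor a before/after comparator and can only be described. The user-experience part, the primary outcome and its analysis are untouched, and the blinding statement is not overturned.

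What is at stake is a randomised comparison with a precision of about ±10.6 points on SURE positivity at its widest. That figure assumes 170 responders per arm and 50% prevalence. The article states no hypothesis or power for this comparison. The point should be fixed, but it is not critical to the trial.

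**What to change.** **Preferred:** amend the sentence in Participant timeline and assessments so that the K-DQI and SURE go to both arms at 6 months, as Table 2 shows. State that SURE positivity and K-DQI scores will be compared between arms. Reserve intervention-only items for questions about using the tool itself. The cost is a small extra burden for about 200 TAU participants, at a contact already scheduled.

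**Alternative, if the questionnaires are meant for tool users only:** mark the Table 2 row I, align Table 3 and the list of regular assessments, and reword the third secondary outcome as a description of tool users, without reference to an effect on decision making. This costs nothing to run but gives up the randomised comparison.

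In either case, state that any fields completed in one arm only are kept out of the blinded analysis file.
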